#### TPT regimen

In Ethiopia, all clinics are participating in IMPAACT4TB where 3HP is being rolled out [20]. All contacts 2 years and older will be initiated on 3HP while children < 2 years will be initiated on 3RH. In South Africa, the clinics are not participating in IMPAACT4TB and all children < 5 years will be started on 3RH. In both countries, if there is a contraindication to initiating rifamycins (e.g., drug interaction including antiretroviral therapy), 6H will be used.

### Sample size considerations

We considered sample size estimation for the South Africa and Ethiopia sites separately because of the differences in TB epidemiology in the two countries. Sample size calculations were based on the primary outcome which is the clinic-level number of child contacts under age 15 years (Ethiopia) or under 5 years (South Africa) initiating TPT per index patient, compared between the two study arms. We expect there to be a harmonic mean of 51 and 32 diagnosed TB patients per clinic during the study period, in South Africa and Ethiopia respectively. We also expect 20% refusals, withdrawals, or loss to follow-up leading to an average of 40 and 26 TB patients, as reported by the respective TB programs. An estimate of the coefficient of variation (CV) was obtained from a previous contact tracing study in South Africa which was 0.35 [6]. We assumed a similar amount of between-cluster variability in Ethiopia, and we also evaluated how the required sample size changed if we considered a slightly higher CV of 0.4. Prior household-based contact tracing studies and 2016 DHS data showed that households of index TB patients in South Africa and Ethiopia, respectively, have 1.8 and 2.1 children under the age of 15, and we expect that 30% would initiate TPT under the standard of care [6, 29–32]. We hypothesize that the intervention would double the number of children per TB patient initiated on TPT — from 0.5 (=1.8×0.3) to 1 in South Africa, and 0.6 (=2.1×0.3) to 1.2 in Ethiopia. A total of 18 (9 per arm) clinics in each country would be required to detect this effect with 80% power at a 5% level of significance assuming a CV of 0.35. A larger CV of 0.4 would require 20 and 22 clinics in South Africa and Ethiopia, respectively.

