### Objectives and endpoints

The primary objective of this study is to determine the effectiveness of home-based contact management, including TPT initiation and follow-up, using community-based healthcare workers to increase TPT initiation as compared to facility-based contact management. The primary endpoint is the cluster-level ratio of the number of household child contacts less than 15 years of age in Ethiopia and less than 5 years of age in South Africa initiated on TPT (3HP, 3RH, or 6H) per index patient, comparing the intervention to the control arm (Table 1). Because we anticipate heterogeneity in the epidemiology of TB and potential differences in the response to the intervention between countries, the primary outcome will be assessed across countries and within countries.

**Table 1 Tab1:** Primary and secondary outcomes for the CHIP-TB trial

**Primary outcome**	**Outcome description**	
TPT initiation among child contacts	The cluster-level ratio of the number of household child contacts less than 15 years of age in Ethiopia and less than 5 years of age in South Africa initiated on TPT per index patient, comparing the intervention to the control arm	
**Secondary outcome**	**Outcome description**	
Child contact identification	The cluster-level ratio of the number of household child contacts less than 15 years of age in Ethiopia and less than 5 years of age in South Africa identified per index patient	
Continuum of care	The cluster-level proportions of estimated child contacts who progress through each stage of the pediatric TB prevention continuum of care (identification, screening, initiation, and completion) overall and by age, by TPT regimen, and by country. *estimated child contacts will be calculated using DHS data	
Treatment completion (as defined by WHO TPT Handbook)	• Proportion of children initiated on TPT who successfully completed TPT • Proportion of children initiated on TPT who were lost to follow-up • Proportion of children initiated on TPT with incident TB (treatment failure) • Proportion of children initiated on TPT who died • Proportion of children initiated on TPT who discontinued TPT due to: toxicity, drug-drug interaction, severe illness (e.g., malaria), pregnancy, or family preference *Treatment completion was defined as 11 doses in 16 weeks for 3HP and 68 doses in 4 months for 3RH [19].	
**Implementation outcome**	**Quantitative assessment**	**Qualitative assessment**

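### South Africa's sample size uses household contacts under 15 although its primary outcome counts only contacts under 5; secondarily, the printed clinic numbers do not follow from the printed inputs at 80% power

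*Protocol article*

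**What the plan says.** Sample size considerations says the calculation rests on the primary outcome, described as the "clinic-level number of child contacts under age 15 years (Ethiopia) or under 5 years (South Africa) initiating TPT per index patient". Objectives and endpoints, Study population and Statistical analysis use the same South African age limit; the endpoint is contacts "less than 5 years of age in South Africa initiated on TPT (3HP, 3RH, or 6H) per index patient".

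The same sample-size paragraph then gives household sizes: "households of index TB patients in South Africa and Ethiopia, respectively, have 1.8 and 2.1 children under the age of 15". It adds that "we expect that 30% would initiate TPT under the standard of care", and assumes the intervention doubles the rate: "from 0.5 (=1.8×0.3) to 1 in South Africa, and 0.6 (=2.1×0.3) to 1.2 in Ethiopia".

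The result is: "A total of 18 (9 per arm) clinics in each country would be required to detect this effect with 80% power", at a 5% significance level and a CV of 0.35. The sensitivity statement is: "A larger CV of 0.4 would require 20 and 22 clinics in South Africa and Ethiopia, respectively".

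Two other places matter. Strengths (Discussion) says the two settings are separately powered. Cluster selection and randomization puts 2019 TPT initiation among contacts under 5 at 33% in Ethiopia and 56% in South Africa.

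**The concern.** Children under 5 are only part of the 1.8 children under 15, so the South African rates belong to a wider population than the one enrolled and analysed. A lower event rate adds Poisson noise to each clinic's ratio. Even if the intervention doubles initiation, the same 18 clinics then have less power than the same calculation gives for the printed rates. The analysis is stratified by country, so a null South African result would be read against an 80% figure that was not derived for that outcome.

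The second issue concerns reproducibility. If the printed clinic numbers do not follow from the printed inputs, a reader cannot tell how much margin 18 clinics provide, or whether a CV of 0.40 really takes the trial below 80% power.

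**Working it through.** **Inputs (Sample size considerations).** Index patients per clinic after 20% loss: m = 40 in South Africa (51 × 0.8 = 40.8) and 26 in Ethiopia (32 × 0.8 = 25.6). Rates r0 to r1: 0.5 to 1.0 and 0.6 to 1.2. CV k = 0.35 or 0.40. Alpha is 5%, taken as two-sided because sidedness is not stated. Power is 80%, with 9 clinics per arm.

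**Formula.** The article names none. The usual one for unmatched cluster trials with rates is, per arm,

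c = 1 + (z_α/2 + z_β)² × [(r0 + r1)/m + k²(r0² + r1²)] / (r1 − r0)².

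With r1 = 2·r0 the fraction reduces to V = 3/(m·r0) + 5k². For 80% power (1.960 + 0.842)² = 7.849, so c = 1 + 7.849·V. Power at 9 per arm is Φ(√(8/V) − 1.960).

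**Step 1: the printed figures.**

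| | V | c per arm | Clinics | Printed | Power at 9 per arm |
|---|---|---|---|---|---|
| South Africa, CV 0.35 | 0.1500 + 0.6125 = 0.7625 | 6.98 | 14 | 18 | 90.0% |
| Ethiopia, CV 0.35 | 0.1923 + 0.6125 = 0.8048 | 7.32 | 16 | 18 | 88.4% |
| South Africa, CV 0.40 | 0.1500 + 0.8000 = 0.9500 | 8.46 | 18 | 20 | 82.7% |
| Ethiopia, CV 0.40 | 0.1923 + 0.8000 = 0.9923 | 8.79 | 18 | 22 | 81.0% |

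A noncentral-t version gives 16 clinics in both countries at CV 0.35, with power of 89.7% and 88.1% at 9 per arm. A gamma-Poisson simulation of the t-test gives 92.5% and 91.0%. Neither comes near 80%.

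**Step 2: settings that do return 18, 18, 20 and 22.** Each row below rounds up to 9, 9, 10 and 11 per arm.

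| Unstated setting | South Africa 0.35 | Ethiopia 0.35 | South Africa 0.40 | Ethiopia 0.40 |
|---|---|---|---|---|
| 90% power, no added cluster | 8.01 | 8.46 | 9.98 | 10.43 |
| 80% power, alpha 0.025, unrounded inputs | 8.12 | 8.59 | 9.90 | 10.37 |
| 80% power, alpha 5%, within-clinic variance twice Poisson | 8.16 | 8.83 | 9.63 | 10.30 |

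**Step 3: South Africa with an under-5 rate.** The number of under-5s per index household, u, is not in the article, so it is an assumption. The 30% baseline, the doubling, m = 40, 9 clinics per arm and the CVs are kept. Then r0 = 0.3u, V = 0.075/r0 + 5k², and expected control-arm starts are 9 × 40 × r0 (180 at the printed 0.5).

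| u | r0 to r1 | Control starts | Power, CV 0.35 | Power, CV 0.40 |
|---|---|---|---|---|
| 0.3 | 0.09 to 0.18 | 32 | 65% | 60% |
| 0.6 | 0.18 to 0.36 | 65 | 79.6% | 73% |
| 0.9 | 0.27 to 0.54 | 97 | 85% | 78% |

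Simulation at u = 0.6 and 0.9 gives 2 to 3 points more, so these figures are approximate. The formula reaches 80% when V = 8/7.849 = 1.019. At CV 0.35 that needs r0 = 0.075/(1.019 − 0.6125) = 0.184, or u of about 0.61. At CV 0.40 it needs r0 = 0.075/(1.019 − 0.800) = 0.342, or u of about 1.14, which is 63% of the 1.8.

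**Step 4: the two issues interact.** Doubling the Poisson term is arithmetically the same as halving r0. If the third setting in Step 2 was used, u = 0.6 has the power shown for u = 0.3: 65% and 60%.

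**The case against.** Several points on the other side have force.

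- **The South African trial is not shown to be underpowered.** A reader might infer that it is, but the documents do not support this, because the under-5 count is missing. At u = 0.6 and CV 0.35 the formula gives 79.6%, practically the printed claim, and at 0.9 it gives 85%. What stands is that the 80% was not derived for the outcome tested.
- **The printed counts are not shown to be a 90% power calculation.** That reading is tempting, but two other unstated settings at 80% power fit equally well. The 90% route is also fragile: using 0.54 (the actual 1.8 × 0.3) in place of 0.5, South Africa at CV 0.35 drops to 7.90 per arm, or 16 clinics. Variance above Poisson is plausible because several children in one household may start together, though the article does not say so. Telling the authors to print 88% and 81% for Ethiopia, or to delete or relabel the CV 0.40 sentence, would impose a formula they may not have used.
- **The clinic-number gap is conservative.** Under the Poisson formula 18 clinics are more than the printed inputs require, so no Ethiopian conclusion is at risk. An article may also condense a fuller derivation. This makes the second issue minor, but the printed inputs, level and power still do not agree with the counts under the standard formula.

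Nothing in the article answers the age mismatch, which lies within a single paragraph.

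**Conclusion.** The age mismatch is established from the text and does not depend on any formula. The South African outcome is under 5, but its planning rate is built on children under 15. The 80% power, and the statement that the settings are separately powered, are unsupported for South Africa.

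The size of the effect is conditional. Under the Poisson-plus-CV formula, power is about 65% to 85% at CV 0.35 and 60% to 78% at CV 0.40 for an assumed 0.3 to 0.9 under-5s per household. Those figures also carry over the 30% baseline and the doubling, which sit badly with the 56% the article quotes for South African contacts under 5. Doubling 56% gives 112%, and the largest possible ratio from that baseline is 100/56 = 1.79. The 56% may have a different denominator from the 30%, so this calls for reconciliation and does not by itself prove an error.

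The clinic-number discrepancy is a secondary, conservative reproducibility problem: 14, 16, 18 and 18 recomputed against 18, 18, 20 and 22 printed. The article does not show which unstated setting produced it.

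**What to change.** 1. Recompute South Africa with the number of contacts under 5 per index household, naming the source. Replace the 0.5-to-1 rates.
2. Reconcile the 30% baseline and the assumed doubling with the 56% initiation given in Cluster selection and randomization for South African contacts under 5.
3. State the resulting power, or the detectable ratio, for the 18 South African clinics at CV 0.35 and 0.40. Bring the separately-powered statement in Strengths into line with it.
4. For both countries, state the formula, alpha and its sidedness, the power, and any added cluster or variance inflation actually used. Then make the 80% power statement and the CV 0.40 sentence agree with them.

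The cost is a recalculation and a few reworded sentences. Clinics are already randomized and enrolment has begun, so no clinics, procedures or analyses change. The South African power figure may become less favourable.

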### Cluster selection and randomization

The clinics chosen in both Ethiopia and South Africa are representative of typical clinics in their respective settings in terms of clinic size, catchment population, HIV co-infection, and provision of TB preventive treatment (Supplementary File 1). TPT initiation is poor in both countries, reaching an estimated 33% and 56% of contacts less than 5 years of age in Ethiopia and South Africa respectively in 2019 [23]. Both countries are part of the IMPAACT4TB project and were rolling out 3HP and/or 3RH for household child contacts [20].

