### Limitations

Prior to study initiation, routine medical records in both South Africa and Ethiopia lacked sufficient detail to be able to collect the necessary data for all primary and secondary outcomes. Study-wide implementation of a child contact management form was needed across intervention and control clinics. Data points were pragmatic and consistent with best practices from the WHO TPT handbook [19]. Healthcare workers will be relied upon to collect these data. We will minimize missing and erroneous data by conducing pre-trial data collection training and by regularly performing data quality checks at each facility and reinforcing training for healthcare workers as needed.

Training of healthcare workers, reinforcement of data collection processes, and the presence of research staff may increase the quality of child contact management in standard of care facilities, which may therefore limit the effect size of the intervention.

In South Africa, research nurses will be hired to conduct the household visits due to overall staff and OTL shortages. This may impact the generalizability of the study results in South Africa. However, this will not be the case in Ethiopia where the health extension workers, employed by the health system, will be implementing the study.

We expect that between-cluster contamination will be limited by country guidelines that require TB patients to seek care at the clinic to which their home is assigned to ensure the clinic’s ability to provide directly-observed therapy for the TB index patient. This, however, is variably enforced by clinics in South Africa where anyone who lives within the catchment area of the study will be treated based on where the index patient sought care. This information will be collected and, if relevant, may be used in sensitivity analyses.

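### The South African sample size assumes 30% uptake that doubles, but the article puts uptake in that endpoint's age group at 56% and does not reconcile the two

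*Protocol article*

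**What the plan says.** Sample size considerations defines the outcome as "the clinic-level number of child contacts under age 15 years (Ethiopia) or under 5 years (South Africa) initiating TPT per index patient". For both countries, "we expect that 30% would initiate TPT under the standard of care". The effect is then set: "We hypothesize that the intervention would double the number of children per TB patient initiated on TPT", that is, "from 0.5 (=1.8×0.3) to 1 in South Africa, and 0.6 (=2.1×0.3) to 1.2 in Ethiopia". Households of index patients are said to "have 1.8 and 2.1 children under the age of 15" in South Africa and Ethiopia respectively. The stated requirement is 18 clinics per country (9 per arm) for 80% power at the 5% level with a CV of 0.35.

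Cluster selection and randomization describes current TPT initiation as "reaching an estimated 33% and 56% of contacts less than 5 years of age in Ethiopia and South Africa respectively in 2019". It calls the chosen clinics "representative of typical clinics in their respective settings in terms of clinic size, catchment population, HIV co-infection, and provision of TB preventive treatment". Limitations adds that training, data-collection support and the presence of research staff "may increase the quality of child contact management in standard of care facilities". Strengths says the two settings are separately powered.

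**The concern.** The South African endpoint is restricted to children under 5, and the only uptake figure the article gives for South African contacts of that age is 56%. The planned intervention-arm uptake (2 × 30% = 60%) is therefore close to what the article reports as usual care. Ethiopia is not affected: its 33% agrees with the 30%, and doubling 33% gives 66%, which is feasible.

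The primary analysis is stratified by country, so South Africa gets its own result. If its true baseline is nearer 56% than 30%, the trial has much less power there than the article implies. A worthwhile gain could then fail to reach significance and be taken for absence of effect.

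**Working it through.** **Inputs from Sample size considerations.** Index patients per clinic after 20% loss: m = 40 (South Africa), 26 (Ethiopia). CV k = 0.35. Clinics per arm c = 9. Rates per index patient: 0.5 to 1.0 and 0.6 to 1.2. A two-sided 5% level is assumed, because sidedness is not stated.

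**Input not in the article.** Under-5 contacts per index patient, h. I take 0.4 to 1.8; the upper end is the article's own under-15 figure for South Africa.

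**Formulae** (unmatched cluster-trial comparison of rates):
- V = (r0 + r1)/m + k²(r0² + r1²)
- Clinics per arm: c = 1 + (1.96 + 0.84)² V/(r1 − r0)²
- Power = Φ(√[(c − 1)(r1 − r0)²/V] − 1.96)

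**Step 1: the plan's own figure.** For South Africa, V = 1.5/40 + 0.1225 × 1.25 = 0.1906, so c = 1 + 7.85 × 0.1906/0.25 = 6.98, or 7 per arm. Ethiopia gives 7.32, or 8 per arm. At a CV of 0.4 the results are 8.46 and 8.79, so 18 clinics in each country against the stated 20 and 22. The stated figures were not reproduced exactly, but they err on the safe side: on the stated inputs, 9 per arm gives about 90% power in South Africa and 88% in Ethiopia (88% by noncentral t).

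**Step 2: the ceiling.** 2 × 56% = 112%, which exceeds 100%. If 56% is the share of all household under-5 contacts who start TPT, the largest possible ratio is 1/0.56 = 1.79.

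**Step 3: power from a 56% baseline.** Set r0 = 0.56h and r1 = h × target uptake, with c = 9, m = 40, k = 0.35. Worked case, h = 0.6, target 80%: r0 = 0.336, r1 = 0.48, V = 0.816/40 + 0.1225 × (0.1129 + 0.2304) = 0.0625. Power = Φ(√[8 × 0.144²/0.0625] − 1.96) = Φ(−0.33) = 37%.

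| h (assumed) | 56% to 80% (ratio 1.43) | 56% to 90% (1.61) | 56% to 100% (1.79) | Ratio detectable at 80% power | Uptake that ratio needs |
|---|---|---|---|---|---|
| 0.4 | 33% | 52% | 69% | 1.95 | 109% |
| 0.6 | 37% | 58% | 75% | 1.86 | 104% |
| 0.9 | 41% | 63% | 79% | 1.81 | 101% |
| 1.8 | 45% | 68% | 83% | 1.74 | 98% |

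A noncentral-t calculation gives almost the same powers.

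**Step 4: how much comes from the baseline and how much from h.** With a 30% baseline that doubles, power is 72% at h = 0.4, 80% at 0.6, 85% at 0.9 and 90% at 1.8. Using an under-15 household size for an under-5 endpoint therefore costs some power by itself. The larger loss comes from the baseline, because a high baseline limits how large the ratio can be.

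**Step 5: the other reading of 56%.** Suppose 56% is the share of identified contacts only. Uptake of 30% among all household contacts would then fit if about 0.30/0.56 = 54% of them were identified. Reaching 60% of all contacts is arithmetically possible, for example with 80% identified and 75% of those started (0.80 × 0.75 = 0.60). On this reading the two figures agree and the doubling is attainable.

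**The case against.** A reader might infer that the article proves the doubling cannot happen in South Africa. It does not.

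- **Denominator.** The 56% is an estimated national figure for 2019, and the article does not say whether it refers to all household contacts or only identified ones. The 30% cites different sources and is applied to all household children.
- **Type of endpoint.** The endpoint is a count of starts per index patient, so it can rise through better identification as well as better uptake. Background says most child contacts are either not identified or not linked to care, and that home-based tracing finds more children under 5. Identification per index patient is a secondary outcome.
- **Population.** The trial enrols contacts of consenting, bacteriologically confirmed adult index patients. Calling the clinics representative does not say that these clinics reach 56%.
- **Assumed household size.** A detectable ratio that needs more than 100% uptake depends on an h the article does not give. At h = 1.8 the ratio is 1.74, just under the ceiling.
- **Reporting.** The analysis section commits to a ratio with a 95% confidence interval, an across-country assessment is also planned, and Limitations already concedes that control clinics may improve. Nothing in the article says an imprecise result would be reported as no effect.

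These points stand, and they make the ceiling conditional. They do not remove the discrepancy. The article describes the 56% as a share of contacts under 5 without qualification, never says it is limited to identified contacts, and gives no reason for using 30% in South Africa. Power for 56% to 80% also stays below one half at every h tried. The 30% is attached to children under 15, but since the South African endpoint is under 5, the 56% is the closer match in age.

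**Conclusion.** The point holds as an unreconciled planning assumption for South Africa, not as proof that the planned effect is unattainable. If 56% applies to all household under-5 contacts, the planned ratio of 2.0 lies above the ceiling of 1.79, power for 56% to 80% is about 33-45%, and 80% power requires a ratio of about 1.74-1.95. These figures rest on 9 clinics per arm, 40 index patients per clinic, a CV of 0.35, a two-sided 5% test and an assumed 0.4-1.8 under-5 contacts per index patient. If 56% covers identified contacts only, a doubling remains open, but the article does not make that argument. The slack in the 18 clinics does not restore 80% power for gains to 80% or 90% uptake from a 56% baseline. At 100% uptake, power passes 80% only towards the upper end of the assumed range. Ethiopia is unaffected.

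**What to change.** 1. Reconcile Cluster selection and randomization with Sample size considerations: state the denominator of the 56%, and say why 30% is used for South Africa.
2. Restate South African power and the ratio detectable at 80% power for the fixed 18 clinics, using under-5 contacts per index patient, at baselines of 30%, 45% and 56%. Give the maximum attainable ratio beside each if the baseline refers to all household contacts: 1/0.30 = 3.33, 1/0.45 = 2.22 and 1/0.56 = 1.79.
3. In Strengths, qualify the statement that the settings are separately powered as regards South Africa, unless the 30% is justified.
4. State that the South African result will be interpreted from its confidence interval, and that non-significance will not be read as no effect.

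The cost is a recalculation and a few sentences. No extra clinics are needed and trial conduct does not change. The downside is a less favourable stated power for South Africa if the higher baseline stands.
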